***2. The background***

Co-infection with food-borne helminthes (such as *Clonorchis sinensis* , hookworm, *Ascaris lumbricoides* and *Trichuris trichiura*) is common in China. As a subgroup of neglected tropical diseases, these soil-transmitting helminthes infections affect nearly 1.4 billion people worldwide. Among these, approximately 129 million patients are Chinese. Owing to the absence of a vaccine, chemotherapy is commonly used to control the coinfection of helminthes. Thus, the selection of drugs is crucial. As to C. sinensis, praziquantel exhibits satisfactory efficacy and becomes the first line drug of choice for clonorchiasis. The recommended treatment regimen by WHO is 25 mg/kg thrice daily for two consecutive days that results in cure rates of 93.5–100%. However, this dose schedule of praziquantel may be difficult to complete in the mass treatment because of multiple treatments and adverse events, while administration of single dose or reduction of treatment course results in less or unstable efficacy. What’s more, although no praziquantel resistance cases are documented, a low cure rate (29%) reported in Vietnam as patients with C. sinensis infection were treated with three daily 25 mg/kg of praziquantel prompted us to pay more attention to the resistance to praziquantel. Therefore, developing the new drugs against C. sinensis is urgent. In addition, praziquantel also exhibits activity against hookworm and 93% cure rate was reported as a single dose of 40mg/kg praziquantel was administrated to patients with hookworm infection. As to soil-transmitting helminthes, imidazole drugs are recommended for treatment by WHO. Among these, mebendazole is a broad-spectrum antihelmintic agent and was reported to be effective against C. sinensis in rats and their single complete curative dose was 150 mg/kg. Similar results were also reported in Xiao’s study. Tribendimidine is abroad-spectrum anti-intestinal nematodes drug. In recent researches, it is proved to be effective to C.sinensis in rats and hamsters. A single dose of 150 and 100 mg/kg tribendimidine resulted in 98% and 100% mean worm burden reduction in the rats and in hamster, respectively. Meanwhile, tribendimidine showed good effective activity to juvenile C. sinensis in hamsters, and the dose of 100mg/kg tribendimidine caused 90.6% mean worm burden reduction. In addition to these laboratory studies, tribendimidine also showed good therapeutic profiles against C. sinensis and Opisthorchis viverrini in clinical trials, and only mild and transient adverse events were reported. Based on the above evidence, we use the praziquantel, tribendimidine and mebendazole to treat the patients with co-infection of helminthes to appraise the efficacy and safety.

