***5. The procedure***

**(1) The study design**: we will perform a randomized, open-label trial to assess the efficacy and safety of praziquantel, tribendimidine and mebendazole against the co-infection of helmithes. All the participants who meet the eligible criteria will be randomly assigned into four groups: Praziquantel will be administrated orally according to regional policy in Hunan: 75 mg/kg in four divided doses (twice daily spaced by 6 h for two consecutive days). Tribendimidine will be given by two means: one is a single dose of 400 mg and the other is 200 mg twice daily spaced by 6 h. Mebendazole will be given 400 mg as a single dose.

In addition, parts of participants who are assigned to be treated with tribendimidine will accept blood and urine routine checks, hepatic and renal function examinations, and electrocardiogram (ECG) examinations before and 24 h after the treatment. The abnormal indexes will be supervised and recorded.

Participants will be asked to report any potential drug-related signs and symptoms at 3 h, 24 h and 48 h after the first dose by the use of a standardized questionnaire.

Three weeks after treatment, participants were asked for two consecutive stool samples.

**(2) Preliminary survey:** To invite the residents aged 15 to 65 who lives in the Dazhongqiao and Sankoutang village , Qiyang country, Hunan province ,P.R.China to participate this trial. The name, age, sex, educational background, race and telephone will be recorded. Participants will receive containers with unique identification numbers and be invited to bring a fresh stool sample the following morning. Stool containers will then be taken to the laboratory at the Qiyang Center of Diseases Control and Prevention (Qiyang CDC). From each stool sample, three Kato-Katz thick smears will be prepared and be quantitatively examined with light microscopy for worm eggs (e.g., C. sinensis, hookworm, A. lumbricoides and T. trichiura). Number of worm eggs are counted and recorded for each parasite species separately. Patients with a microscopically confirmed co-infection with helminthes will be asked for a second stool sample.

**(3) Sample size.** Sample size was based on a suggested sample size of 12 patients per group for proof-of-concept trials. Taking into account of the patients dropping out, we will plan to enroll 40 participants per group.

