**(9) Follow up:** The trial clinicians will be present, monitor acute adverse events, and provide medical assistance if necessary. Participants will be asked to report any potential drug-related signs and symptoms at 3 h, 24 h and 48 h after the first dose by the use of a standardized questionnaire. Intensity of AEs are recorded and graded as mild, moderate, severe and serious as judged by study physicians.

Mild: asymptomatic or mild symptoms; clinical or diagnostic observations only; intervention not indicated

Moderate: minimal, local or noninvasive intervention indicated.

Severe: severe or medically significant but not immediately life-threatening; hospitalization or prolongation of hospitalization indicated.

Serious: life-threatening consequences; urgent intervention indicated.

**(10) Re-examination of the stool sample**: Three weeks after treatment, participants were asked for two consecutive stool samples. Stool containers will then be taken to the laboratory at the Qiyang Center of Diseases Control and Prevention (Qiyang CDC). From each stool sample, three Kato-Katz thick smears will be prepared and be quantitatively examined with light microscopy for worm eggs (e.g., C. sinensis, hookworm, A. lumbricoides and T. trichiura). Number of worm eggs will be counted and recorded for each parasite species separately.

**(11) Primary and secondary outcomes:** Primary outcomes are the cure rate (CR) and egg reduction rate (ERR) at 3 weeks after treatment as efficacy outcomes. The CR is defined as the percentage of participants excreting eggs before treatment who became negative after treatment. The ERR is calculated as the reduction in the group’s geometric mean egg count after treatment divided by the geometric mean of the same patients before treatment, multiplied by 100. Secondary outcomes are the frequencies of adverse events (AEs) and the abnormal biochemical tests after treatment including urine and blood test, hepatic and renal function examinations and ECG.

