***6. The second treatment***

Based on first treatment results, we may carry out the second treatment with the same procedure and same clinical practices, hoping to enhance the efficacy.

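### No adverse-event question is scheduled after 48 h from the first dose, although participants are contacted again at three weeks

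*Protocol*

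**What the plan says.** Section 5(1) of the protocol sets the safety questioning: "Participants will be asked to report any potential drug-related signs and symptoms at 3 h, 24 h and 48 h after the first dose". Section 5(9) repeats the schedule, "at 3 h, 24 h and 48 h after the first dose by the use of a standardized questionnaire", and adds "The trial clinicians will be present, monitor acute adverse events, and provide medical assistance if necessary", with no statement of how long the clinicians stay. Neither section, nor any other, schedules a later question on adverse events.

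For part of the tribendimidine participants, section 5(1) also plans laboratory tests and "electrocardiogram (ECG) examinations before and 24 h after the treatment". Abnormal values are to be monitored and documented; no repeat test or end date is given.

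The next planned contact is in section 5(10): "Three weeks after treatment, participants were asked for two consecutive stool samples". Only stool collection and egg counting are described there.

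Section 5(11) defines the safety outcomes without a time window: "Secondary outcomes are the frequencies of adverse events (AEs) and the abnormal biochemical tests after treatment". Section 6 then provides for possible re-treatment: "Based on first treatment results, we may carry out the second treatment with the same procedure and same clinical practices". It does not say which results are meant.

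**The concern.** Safety stands beside efficacy in the objective (section 1). The adverse-event outcome in section 5(11) carries no time limit, so a reader of the results could take it to cover follow-up to three weeks. The data behind it come from scheduled questions that stop at 48 h.

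Two kinds of information have no planned place on a form: an event that begins between 48 h and three weeks, and what became of an event still present at 48 h. The second bears on how the results would be read beside section 2, which says of earlier clinical trials of tribendimidine that "only mild and transient adverse events were reported". This trial can describe duration only for events that end within its 48 h window.

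This is a matter of data collection. An analysis plan can say how to tabulate answers, but it cannot recover answers to questions that were not asked. It also matters for section 6, because a second treatment may be considered after a period in which no safety question was scheduled.

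**Working it through.** The plan states no figure on this point, so there is none to reproduce. The check sets the schedule out in time and then shows what an assumed rate of late events would imply.

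**Inputs from the protocol**
- Adverse-event questions: 3 h, 24 h and 48 h after the first dose (5(1), 5(9)).
- Stool contact: three weeks after treatment (5(10)), taken here as 21 days from the first dose, 21 × 24 = 504 h.
- Group size: 40 in each of four groups, 4 × 40 = 160 (5(1), 5(3)).

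**Coverage of the interval**
- Share within scheduled questioning: 48 / 504 = 9.5%.
- Time without a scheduled question: 504 − 48 = 456 h = 19 days, or 456 / 504 = 90.5%.

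**What reaches the adverse-event outcome if the plan is followed exactly**
- Starts and ends within 48 h: can be picked up at 3 h, 24 h or 48 h, and its disappearance can be seen at a later one of these contacts.
- Starts within 48 h and still present at 48 h: recorded and graded; later course and outcome have no planned record.
- Starts after 48 h: no scheduled question; recorded only if the participant reports it unprompted.
- Abnormal laboratory or ECG value at 24 h in a tested tribendimidine participant: to be monitored, without a stated end point or final assessment.

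**Illustration (rates assumed; the protocol gives none)**

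Let p be the proportion of participants with an event starting after 48 h. The expected number per arm is 40p, the expected total is 160p, and the chance of at least one in an arm is 1 − (1 − p)^40.

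| p | Expected per arm of 40 | Expected of 160 | At least one in an arm |
|---|---|---|---|
| 1% | 0.4 | 1.6 | 33% |
| 2% | 0.8 | 3.2 | 55% |
| 5% | 2 | 8 | 87% |
| 10% | 4 | 16 | 99% |

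The gap in the schedule does not depend on p; only its practical weight does.

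**The case against.** The strongest reply is that 48 h is a deliberate choice for courses of one or two days. It is stated identically in two places and contradicts nothing else in the protocol, and the documents contain no evidence that late events occur. This stands: the point is an improvement to the design and does not allege an inconsistency.

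Several stronger readings are tempting, and the documents do not support them:

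- **Symptoms present at 48 h are lost.** They are not. The 48 h questionnaire asks about them and section 5(9) has their intensity graded. Only what follows is uncollected.
- **The trial cannot show that any event resolved.** It can, for events reported at 3 h or 24 h and gone by 48 h. The planned outcome is also frequency, and duration is not a stated endpoint.
- **Abnormal tests are dropped after 24 h.** Section 5(1) calls for their monitoring and sets no end. What is missing is a defined final assessment.
- **The second treatment is decided without safety data.** Section 6 neither includes nor excludes them, so this would be inference.
- **A participant with a late reaction could be re-treated unchecked.** Section 6 repeats the procedure of the first course. That plausibly brings back the pre-treatment check-up in 5(7) and the exclusions in 5(5), so a current problem could be noticed. A late reaction that had already resolved might still go unmentioned, and the check-up is not described as recording first-course adverse events.
- **About 90% of events are missed.** The 90.5% is calendar time. It would equal the share of events only if risk were even over 21 days, which nothing in the documents supports for such short courses.

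It may also be objected that section 5(10) does not say who meets the participants at three weeks, so the ease of adding a form there is plausible but not documented. That is fair, and it affects the cost more than the need.

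**Conclusion.** The point holds in a limited form. Followed as written, the protocol has no scheduled route by which events starting after 48 h, or the later course of events open at 48 h, reach the adverse-event secondary outcome, although a contact at three weeks is already planned. Section 6 leaves open whether safety data inform the second treatment.

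The firm part is the schedule: 456 of 504 h carry no adverse-event question. The number of events affected is unknown. The range of 0.4 to 4 per arm (1.6 to 16 of 160) rests wholly on assumed rates of 1% to 10% and counts late-onset events only. A single figure such as 8 of 160 should not be read as an estimate. Sample size and the efficacy outcomes are unaffected. This is a cheap improvement to the safety answer and does not invalidate the plan.

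**What to change.** 1. In section 5(10), add the existing standardized questionnaire to the three-week stool collection. It should ask about new events since the 48 h contact and record the outcome, with a resolution date where known, of any symptom or abnormal test still open at its last check.
2. In section 5(11), state the window of each adverse-event summary. Keep 0–48 h for the comparison between groups, and tabulate the three-week answers separately, with the number who answered as denominator.
3. In section 6, state whether the first-treatment results include safety data, and have the three-week answers available when the second treatment is considered. Who may be re-treated is a clinical matter on which this point makes no proposal.

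The cost is a short extra form at a contact already planned, provided that someone able to take the answers is present. Recall over about 19 days is weaker than at 48 h, which is why the two periods should not be pooled. Events reported before 48 h are unaffected.

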**(12) Statistical analysis.** All data will be double entered, and the per-protocol analysis will be pursued. Statistical analyses will be done with SAS software (version 9.1). The numbers of every kind of worm eggs recorded from 6 Kato-Katz slides before and after treatment will be added to calculate the arithmetic mean of eggs per gram of stool (EPG) for every participant. The arithmetic means is used to determine the infection intensity, and the geometric EPG is calculated to assess the egg reduction rate among the treatment groups. Logistic regression models will be used to examine cure rates of helminthes in different treatment groups. Negative binomial regression analysis will be adopted to compare egg reduction rates of helminthes between four groups. Pearson’s χ2 test will be applied to compare the proportion of reported adverse events between the treatment groups. Negative binomial regression models will be used to compare the number of adverse events in the treatment groups.

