***9. Preparation for the AEs***

In order to deal with the possible cases of severe adverse reaction caused by the treatment, cooperative hospital should prepare an ambulance. When it is necessary, the ambulance will immediately rush to the scene. Some drugs will be prepared, such as epinephrine injection, antihistamine, antiemetic, antipyretic analgesic, antispasmodic drugs and other conventional aid medicines.

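### 'Serious' is the top step of an intensity scale and is limited to life-threatening events, so a hospitalisation that is not immediately life-threatening cannot be recorded as serious

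*Protocol*

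**What the plan says.** Protocol section 5(9), Follow up, sets the scale: "Intensity of AEs are recorded and graded as mild, moderate, severe and serious as judged by study physicians". The two upper steps are defined as follows:

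- Third step: "Severe: severe or medically significant but not immediately life-threatening; hospitalization or prolongation of hospitalization indicated".
- Fourth step: "Serious: life-threatening consequences; urgent intervention indicated".

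Section 5(11) places safety among the secondary outcomes: "Secondary outcomes are the frequencies of adverse events (AEs) and the abnormal biochemical tests after treatment".

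Section 5(12) plans two comparisons of adverse events. A Pearson χ² "test will be applied to compare the proportion of reported adverse events between the treatment groups". For counts, "Negative binomial regression models will be used to compare the number of adverse events in the treatment groups". Neither mentions grade or seriousness.

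The only other text on grave events is in section 9: "In order to deal with the possible cases of severe adverse reaction caused by the treatment, cooperative hospital should prepare an ambulance". It deals with emergency preparation. It neither defines a serious event nor says how one is recorded.

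**The concern.** Intensity and seriousness are different properties of an event. Intensity says how strong it was. Seriousness says whether it had a grave consequence, such as death, a threat to life or a stay in hospital. An event can be high on one and low on the other, so each needs its own field. Here the protocol announces an intensity scale and then uses 'serious' as the name of its highest step. Seriousness becomes one value of the intensity grade and has no item of its own.

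What is at stake is what the trial can say about grave harms. Safety is named in the objective (section 1) beside efficacy. Under these definitions a statement that no serious adverse event occurred could be true by the protocol's own wording even though participants had been hospitalised. A reader who takes 'serious' to include hospitalisation would be misled. The trial is open-label and the grade is a physician's judgement. Whether an event reaches the top step thus turns on an unblinded judgement about threat to life, while hospitalisation, which is easier to verify, does not move an event into that step.

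**Working it through.** The point is about definitions, and the protocol states no figure to reproduce. The check applies the definitions in section 5(9) to three kinds of event and then looks for another route to a serious-event count.

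**Step 1: apply the scale.**

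| Event | Step that fits | Recorded as serious? |
|---|---|---|
| Hospitalisation indicated, not immediately life-threatening | Third, 'severe', which contains "hospitalization or prolongation of hospitalization indicated" | No |
| Hospitalisation indicated, immediately life-threatening | Fourth, because the third step excludes immediate threat to life | Yes |
| Fatal | No step names it | Undetermined |

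The first row is the defect. The wording leaves no choice: the event meets the third definition and does not meet the fourth.

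**Step 2: look for a second definition.** Sections 5(11) and 5(12) refer to adverse events as a whole. Section 8 covers training, form signatures and slide re-examination. Section 9 covers an ambulance and emergency drugs for 'severe' reactions. None of them defines seriousness or provides a separate item for it. The grade in section 5(9) is the only basis for a serious-event count.

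**Step 3: ask whether the analysis could repair it.** Pooling the third and fourth steps would not isolate hospitalisations. The third step also takes in medically significant events. Both upper definitions are written in terms of what is indicated, not of what happened, and the fourth carries no hospitalisation flag. If the form records only this grade, the information cannot be recovered from it later.

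**Step 4: trace the effect on the planned tests.** The χ² test and the negative binomial model use all adverse events. A hospitalised event enters each in the same way whether it is called 'severe' or 'serious'. The effect on both tests is nil.

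**Step 5: size.** A magnitude would need an expected rate of hospitalised or fatal events, and the protocol gives none. With the planned 40 participants per group (section 5(3)), one participant with such an event would be 1/40 = 2.5% of a group, shown as 0/40 = 0% serious. This assumes one event for illustration and is not a forecast.

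**The case against.** The strongest reply is that no planned result depends on the label. The secondary outcome is the frequency of adverse events, and both comparisons use all of them. The protocol plans no serious-event rate or test and promises no statement that none occurred. Hospitalised events are also not lost: they are graded, and a table by grade that prints the definitions would show them one row below the top. The protocol defines its own term openly and cites no standard that it breaks. With clinicians present and about 160 participants, a death would hardly go unnoticed for want of a label. The background reports only mild and transient events for tribendimidine in clinical trials.

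Much of this stands. The planned tests are untouched, and the missing fatal grade is a narrow gap. Under-reporting is conditional: it arises only if serious events are counted from this grade. But the visibility argument is only partly right, because the 'severe' row mixes hospitalisations with other medically significant events. Nor does defining the term openly help when the definition sits on a scale announced as intensity and leaves seriousness without a field. The mild-events remark concerns one of the three drugs; for praziquantel the background mentions adverse events without giving their severity or rate.

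**Conclusion.** The point holds in a limited form. Section 5(9) fixes a scale on which a hospitalised event that is not immediately life-threatening is 'severe' and cannot be recorded as serious. It has no step for death, and nothing else in the protocol records seriousness. A serious-event count drawn from this grade would omit every such hospitalisation. How many that would be cannot be worked out from the protocol.

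A reader might infer three stronger things that the text does not support:

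- That no hospitalised event can ever be serious. One that is also immediately life-threatening is graded 'serious'.
- That the protocol's adverse-event comparisons are biased. They do not use the grade.
- That serious harms will be under-reported by a known amount. This depends on how a later report counts them, and 2.5% is only one assumed event over 40.

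The conclusion assumes that the form follows section 5(9) as written and has no seriousness item that the protocol fails to mention. This is a fault in a stated definition and not a detail left to the analysis plan, because it governs what is written down when the event occurs. It should be corrected before data collection.

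**What to change.** Make four changes to section 5(9) and to the adverse-event form:

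1. Keep the existing definitions as intensity grades and rename the fourth 'life-threatening'.
2. Add a fatal grade.
3. Record seriousness as a separate yes/no item, answered yes for death, threat to life, or hospitalisation or its prolongation.
4. Report intensity and seriousness separately by arm.

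Section 9 should then use the same terms, so that 'severe' there has the meaning it has in section 5(9).

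The cost is relabelling and one more item on the form. The number of serious events may come out higher than under the present labels. The planned tests stay as they are, and no treatment or emergency procedure changes.

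### The primary egg reduction rate is defined on geometric means but compared between arms by a model for arithmetic means, so its p-value belongs to a different quantity

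*Protocol*

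**What the plan says.** Protocol section 5(11) names two primary outcomes at 3 weeks, the cure rate and the ERR. The ERR is built from the group's "geometric mean egg count after treatment divided by the geometric mean of the same patients before treatment, multiplied by 100". The cure rate rests on zero counts: "The CR is defined as the percentage of participants excreting eggs before treatment who became negative after treatment".

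Section 5(12) confirms the scale of the ERR: "the geometric EPG is calculated to assess the egg reduction rate among the treatment groups". It gives the arithmetic mean another job: "The arithmetic means is used to determine the infection intensity". It then names the between-group method: "Negative binomial regression analysis will be adopted to compare egg reduction rates of helminthes between four groups".

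Neither section says how a zero count enters the geometric mean. Section 5(3) sets the group size: "we will plan to enroll 40 participants per group".

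**The concern.** Two explicit statements do not fit together. The ERR that will be reported is a ratio of geometric means. A negative binomial model with its usual log link describes the log of the expected count, so its group contrasts are ratios of arithmetic means. The p-value printed beside the primary ERR would therefore test something else.

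The difference matters for egg counts after treatment, which mix zeros (the cured) with positive counts (the uncured). The geometric mean is pulled down strongly by the zeros and responds little to high residual counts. The arithmetic mean is driven by those residual counts. An arm that cures many but leaves the rest heavily infected can lead on one scale and trail on the other. A report could then show one arm with the higher primary ERR next to a significant test in favour of the other.

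**Working it through.** **Plan's own figure.** There is none to reproduce. The protocol gives no egg counts, no target ERR and no effect size for the ERR.

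**Inputs.** From the protocol: 40 per arm (5(3)), the geometric definition (5(11), 5(12)) and the named model (5(12)). Assumed: all egg counts, the offset c, and the log link.

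**Formulas.**
- Geometric mean with offset c: GM = exp(mean of ln(x + c)) − c.
- Geometric ERR = 100 × (1 − GM after / GM before).
- Arithmetic ERR = 100 × (1 − mean after / mean before).

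**Illustration 1.** Everyone starts at 500, so the mean before treatment is 500 on either scale. After treatment, arm A has 24 at zero and 16 at 400. Arm B has none cured, with 40 counts spread evenly over 20–60 (mean 40).

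- Geometric, c = 1, arm A: mean log = (16/40) × ln 401 = 0.4 × 5.994 = 2.398; GM = exp(2.398) − 1 = 10.0; ERR = 98.0%.
- Geometric, c = 1, arm B: mean log = 3.667; GM = exp(3.667) − 1 = 38.1; ERR = 92.4%.
- Arithmetic: A has mean 16 × 400/40 = 160, ERR = 68%; B has mean 40, ERR = 92%.
- Negative binomial fit to the after-treatment counts: rate ratio B/A = 40/160 = 0.25, p = 0.001.

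The reported ERR ranks A first. The test favours B.

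**Same data, different offset (c = 24).**

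- A: mean log = 0.6 × ln 24 + 0.4 × ln 424 = 0.6 × 3.178 + 0.4 × 6.050 = 4.327; GM = exp(4.327) − 24 = 51.7; ERR = 89.7%.
- B: mean log = 4.141; GM = exp(4.141) − 24 = 38.9; ERR = 92.2%.

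The geometric ranking now favours B, so the unstated offset alone can decide the order.

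**Illustration 2.** Baseline 200. A has 28 cured and 12 unchanged; B has everyone at 50.

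- Geometric (+1): A has mean log 0.3 × ln 201 = 1.591, GM = 3.9, ERR = 98.0%; B has ERR = 75.0%.
- Arithmetic: A 1 − 60/200 = 70%; B 1 − 50/200 = 75%.
- Negative binomial: rate ratio B/A = 50/60 = 0.83, 95% CI 0.36 to 1.96, p = 0.68.

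Here only the point estimates reverse; the test shows no difference.

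**How often the directions disagree.** Simulated trials, 300 per scenario, 40 per arm, lognormal baseline (mean 500, log-SD 1.2), +1 offset. Residual means the fraction of the baseline count left in the uncured.

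| Cure rate, A vs B | Residual, A vs B | Directions disagree | Disagree and p < 0.05 |
|---|---|---|---|
| 60% vs 10% | 80% vs 15% | 92% | 35% |
| 40% vs 30% | 50% vs 30% | 47% | 5% |
| 80% vs 30% | 30% vs 30% | 2% | 0% |

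The model was fitted to after-treatment counts without baseline, so some of the disagreement reflects chance baseline differences between arms.

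**Zeros.** A geometric mean without an offset is 0 as soon as one count is 0. The chance of at least one cure among 40 is 1 − (1 − CR)^40: 98.5% at a cure rate of 10%, and above 99.99% at 29%, the figure in section 2 ("a low cure rate (29%) reported in Vietnam"). Some handling of zeros is therefore needed in nearly any arm with activity.

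**The case against.** **Zero handling is a detail for the SAP.** This largely stands. A reader might infer that the ERR as written equals 100% in every arm with a cure and so cannot separate arms. The literal formula does give that, but the first calculation would force any analyst to add an offset, and a SAP could state it. The reading is also incompatible with the ranking conflict, which needs an offset before the geometric ERR can rank such arms at all. What remains is narrower: the offset should be fixed in advance, because it can change the order of arms.

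**The conflict is contrived.** This stands in part. A reader might infer that ERR and p-value will commonly point in opposite directions. The working does not support that. Illustration 2 gives no significant reversal. In the simulations, significant disagreement was frequent only in the extreme scenario and absent when one drug cured more with equal residual counts. All counts are assumed.

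**The geometric ERR is a legitimate choice.** This stands. It damps a few very high counts. The fault is the pairing with the named test, not the scale itself.

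**The consequences are limited.** This also stands. The cure rate has its own logistic model and is unaffected. The group size rests on a proof-of-concept rule, not on power for the ERR, and both forms of the ERR can be computed from the recorded counts.

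None of this removes the mismatch. An offset does not cure it, and a SAP could do so only by changing either the definition in 5(11) or the test in 5(12).

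**Conclusion.** The point holds as a mismatch between a primary outcome's definition and its named test. It follows from the text of 5(11) and 5(12) and needs only the standard log link; it does not depend on any assumed count.

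Its size does depend on assumed counts. In illustration 1 the ERR favours A by 98.0 − 92.4 = 5.6 percentage points on the geometric scale and B by 92 − 68 = 24 points on the arithmetic scale, with p = 0.001 for B. A conflict of this kind needs one arm to cure more while its uncured keep higher counts. The illustrations also use the full 40 per arm. Counts are recorded by species, so fewer participants may contribute to the ERR for a given species, and a significant reversal would then be harder to reach.

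Severity: should-fix. The mismatch affects one of two primary outcomes, but the data collected are sufficient and the repair is in the wording.

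**What to change.** Amend 5(11) and 5(12) together, before any outcome counts are seen, in one of two ways.

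1. **Arithmetic primary.** Define the primary ERR as 100 × (1 − arithmetic mean after / arithmetic mean before). Estimate it, with its interval, from the negative binomial model with baseline counts accounted for. Report the geometric ERR as secondary, as exp(mean of ln(EPG + 1)) − 1 after versus before, with a bootstrap interval.
2. **Geometric primary.** Keep the geometric ERR, state the offset, and compare arms by a method on that scale: an analysis of log(EPG + 1), or a bootstrap of the difference in ERR.

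Either is sound. The first keeps the model already named; the second keeps the definition already written.

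The cost is a few sentences, with no extra data or visits. The downside of the first option is that the arithmetic ERR may look less favourable and be less precise. The downside of the second is that the result still depends on the chosen offset and gives little weight to participants who remain heavily infected.
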